#### PEONY (control)

PEONY (Positive Emotion Orientation for Nurturing Your Relationship) is a positive affect enhancement program based on the IRISS intervention [45], adapted to be administered to couples and to be attention-matched in both format (i.e., hybrid group and dyadic sessions) and time spent in intervention. PEONY group sessions present couples with a didactic overview of positive emotion skills, the function of emotions, and general emotional literacy. Couples then learn and discuss specific positive emotions skills: identifying and capitalizing on positive emotions, gratitude, identifying personal strengths, self-compassion, positive reappraisal, acts of kindness, healthy goal setting, behavioral activation, and practicing mindfulness. Two facilitators reinforce content through structured conversations and guided practice, emphasizing unique opportunities to enact skills as a dyad and benefits to incorporating positive affect skills into relationships.

Following group sessions, couples attend two individualized skills coaching sessions with one of their initial group facilitators; these sessions emphasize skills practice and reinforce previously introduced content. In addition to targeted skills practice, couples participate in exercises designed to promote positive reminiscence of their history as a couple and to highlight positive aspects and specific strengths of their relationships. Participants are also provided with a series of “couple scenarios,” which describe common stressors faced by male couples, and then practice applying specific positive emotion skills that might reduce the negative impact of these stressors.

PEONY teaches tangible positive affect skills with a demonstrated benefit of reducing psychological distress for numerous populations; however, these skills do not address or incorporate the primary mechanisms of change emphasized in the 2GETHER intervention. By design, PEONY does not incorporate or prompt communication or sexual health negotiation skills. Through training, supervision, and fidelity monitoring, PEONY facilitators are further discouraged from the unprompted addressing of couples’ communication and sexual health skills to avoid content contamination across study conditions.

### Facilitator training, fidelity, and supervision

All intervention facilitators hold a bachelor’s degree or higher and have direct experience working in social service or research settings with MSM and/or young adults. Our hiring processes prioritize community-based and direct service experience, including HIV testing and counseling, sexual health education, mental health counseling, workshop facilitation, and program coordination. Employing bachelor-level facilitators with relevant community-based experience (as opposed to licensed mental health professionals) helps to ensure the program is easier to implement in community settings.

All facilitation staff are cross-trained in control and active condition components and are expected to facilitate both conditions. Each facilitator completes an intensive 8-week training protocol, which includes communication skills coaching, HIV risk reduction, medication adherence counseling, and session-specific intervention content for each condition. As part of training, all facilitators complete mock session run-throughs with the principal investigator, co-investigator/supervision lead, and project coordinator for feedback. Facilitators conduct additional mock sessions with professional patient simulators to further develop skills training. Through patient simulation, facilitators gain “real life” session experience where they learn how to lead effective communication practice among dyads and handle challenging or emotionally volatile situations. Additionally, staff participate in periodic “booster” trainings throughout the study to advance their facilitation skills, including motivational interviewing, harm reduction, and mindfulness training.

Facilitators receive weekly supervision through review of their audio-recorded 2GETHER skills coaching sessions. Supervision is principally provided by one of three doctoral-level clinical psychologists and a master-level HIV test counselor in a group setting. During group supervision, pertinent audio segments are played to highlight areas for improvement and reinforce facilitators’ skillful handling of difficult situations. Once facilitators master 2GETHER content, they are invited to provide peer supervision to fellow facilitators. Supervision for the control condition is conducted separately using an analogous format and led by a PhD-level positive emotions project manager and a master-level project coordinator trained in both active and control condition content. Given that this trial uses the same facilitators across conditions, supervision also aims to minimize drift in content across conditions and promote fidelity.

To further ensure fidelity to the intervention protocol and minimize contamination across study conditions, facilitators audio-record all 2GETHER and PEONY sessions. Twenty percent of sessions (both group and individualized couple sessions) are randomly selected for review by an independent assessor to monitor content delivery. All staff members trained in intervention delivery assist with fidelity monitoring. To minimize bias, facilitators are eligible to conduct fidelity assessments only for participants with whom they did not work in sessions. Fidelity monitoring assessors complete a binary checklist indicating whether the essential components of each intervention session were completed effectively by facilitators. In addition, assessors rate facilitator time management, completion of session activities, addressing of participant concerns and questions, participant engagement, and familiarity with session materials and content.

### Participant retention

All randomized participants complete follow-up assessments at 3, 6, 9, and 12 months post-intervention. For 3-, 6-, and 9-month assessments (which occur remotely), participants are emailed a survey link 1 week prior to their target follow-up date and receive regular survey completion reminders from study staff by phone, email, and text. Participants who do not complete a survey within 6 weeks of their target date do not have their responses recorded for that corresponding follow-up point but are eligible to complete future follow-up assessments unless they withdraw from the study. Analogous procedures are used to schedule and engage participants in the 12-month in-person assessment.

In addition to conducting persistent retention reminders across a variety of media, study staff engage in a multitude of strategies to encourage participant completion of follow-up assessments. All participants receive $50 for each completed follow-up assessment as compensation for their time and to facilitate their ongoing participation. Participants also receive a majority of their retention contacts from the same, central staff member throughout the duration of the study to enhance clarity and build rapport. If a participant becomes disengaged, they may be additionally contacted by one of the facilitators of their previous intervention sessions to encourage re-engagement.

If relationships dissolve during the course of the study, participants are encouraged to continue to complete all remaining follow-up assessments as individuals. When completing as an individual, the couple communication task is eliminated from the 12-month follow-up. Furthermore, single participants do not complete questions in the self-report survey assessing current relationship functioning, but they complete additional questions assessing the impact of their relationship dissolution on their health and wellbeing. If a participant indicates they have a new romantic partner during the follow-up period, that partner is given the opportunity to complete a one-time self-report survey. This new romantic partner is also compensated $50 for their responses and time.

### Protocol changes after trial launch

We made two protocol changes after study launch to address barriers that arose with regard to participant enrollment, scheduling, and safety. Both of these protocol changes were facilitated by integrating eHealth strategies into the study that had previously been developed for an online RCT of 2GETHER, described elsewhere [30]. First, we experienced difficulties with enrollment as a result of many couples having very limited availability for group sessions. To address this, we modified the protocol to allow couples to be randomized as a group of “1” if they were unable to attend the next three scheduled group cohorts after completing baseline. For couples who participate individually (i.e., not in a group), we modified the format of the group sessions in order to reduce fatigue that would result from presenting didactic content to one couple for several hours at a time. Based on the protocol from our online version of 2GETHER [30], we provide couples with all didactic content prior to sessions 1 and 2, in the form of self-paced, narrated videos. Thus, sessions 1 and 2 can instead focus on content review and discussion. Sessions 3 and 4 (i.e., skills practice sessions) were not modified for this protocol change as these were already individualized couple sessions.

Second, the onset of the COVID-19 pandemic in March 2020 spurred us to develop remote protocols for all study activities in order to ensure the safety of our participants and staff. Given that we were already in the process of evaluating an online version of 2GETHER [30], the adaptation of the current protocol was relatively straightforward. In the online version of 2GETHER, all sessions are completed via videoconference (e.g., Zoom). Similar to the protocol described above for couples participating in groups of 1, couples are emailed links to self-paced, narrated videos of the didactic content 1 week prior to each of the group sessions, and group sessions focus on content review and discussion. The protocols for sessions 3 and 4 were not altered for online administration, except that they are now conducted remotely via videoconference. With regard to baseline and 12-month follow-up assessments (other interim time points were already completed remotely), we have made several protocol changes to allow for remote data collection. Participants are sent links to their self-report surveys, hosted via REDCap. Couples are also provided instructions for self-recording their couple communication task via Zoom. Finally, participants are mailed STI testing supplies from Molecular Testing Labs® for self-collection of specimens. Participants ship specimens back to the lab, the lab provides study staff with test results, and study staff communicate results to participants. We experienced a lag between the onset of the pandemic in March and the establishment of an agreement with Molecular Testing Labs® in July 2020. Participants scheduled for a baseline or 12-month assessment during this time period completed all assessment components except for STI testing.

### Analytic plan

#### Power analysis

At the onset of this trial, we aimed to randomize 200 dyads (*N* = 400) to the active or control condition and powered our trial based on that enrollment goal. We experienced various challenges to attaining this recruitment goal (primarily those described in the preceding section related to scheduling couples into group sessions and challenges during the COVID-19 pandemic), so we adjusted our recruitment goal based on a second power analysis. This power analysis was conducted using WebPower in R for a cluster randomized trial with two arms. This method allowed us to account for the similarity between members of the same couple. We assumed a conservative intra-class correlation between members of the same couple of 0.5 for the purpose of calculating power. With an adjusted goal of randomizing 125 dyads (*N* = 250), power for the present study will be 0.89 to detect a medium-sized effect and 0.99 to detect a large effect for the differences between the two study arms.

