**Discussion:**

2GETHER is innovative in that it places an equal emphasis on relationship skill building and HIV prevention. Thus, the program has the potential to impact numerous health-related outcomes. Despite challenges related to the recruitment of couples and the COVID-19 pandemic, we were able to enroll a robust sample of young male couples with sufficient power to detect effects on study outcomes.

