## Method

We are conducting an attention-matched RCT to test the efficacy of 2GETHER relative to a control condition based on a well-validated positive affect enhancement program [38]. We selected a highly active and attention-matched control condition that is not theoretically linked to HIV risk behaviors. We aim to randomize 200 dyads (individual *N* = 400) to the 2GETHER intervention or control, and we will examine primary and secondary outcomes at 12 months post-intervention, with interim follow-up at 3, 6, and 9 months post-intervention. There were no restrictions regarding receipt of concomitant care during the trial.

The primary HIV risk behavioral outcome will be the occurrence of condomless anal sex acts with serodiscordant or unknown status partners (all casual sex partners will be considered unknown status), and we will account for the reduced risk of condomless anal sex in the context of PrEP use and undetectable viral load (e.g., condomless sex while one has an undetectable viral load may be considered no risk). The primary biomedical outcome will be STI incidence (i.e., urethral/rectal Chlamydia and Gonorrhea), a robust biological indicator of HIV risk. Primary dyadic outcomes will be partner relationship agreement concordance and agreement breaks. Secondary HIV-related outcomes will be indicators of engagement in the HIV continua of prevention and care, including HIV testing (HIV-negative and unknown status participants) and antiretroviral therapy adherence for HIV-positive participants. Exploratory outcomes will be PrEP uptake and adherence (for HIV-negative participants) and viral load (for HIV-positive participants). We will test for dose effects and decay in effects over time, and we will examine relationship functioning as mediators of change in HIV transmission risk. Unless otherwise noted, all outcomes will be measured at the individual level (not couple-level). This is advantageous because HIV risk may also occur with partners outside the relationship. Also, relationships may dissolve during the follow-up period, so measuring individual-level outcomes allows us to examine the effects of 2GETHER behaviors after relationship dissolution. 

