### Randomization to the treatment arm

The original plan for randomizing participants was to randomize each couple to either the active or control condition immediately after both members of the dyad completed the baseline assessment using a stratified randomization scheme within blocks of four. After the trial launch in August 2017, we quickly encountered substantial difficulty in randomizing at the couple level; because the first two sessions of the interventions occur in groups, a large enough number of couples would need to complete baseline within the same timeframe, and these couples’ schedules would all need to align in order to convene group sessions. Because of this, we altered the randomization strategy to randomize at the group level. To achieve this, each couple provides their availability for a set of pre-scheduled group sessions occurring over the subsequent 3 months. Once at least two couples sign up for a group session (six couples maximum), all couples within that group are randomized to the active or control condition. All couples must attend their first group session within 3 months of completing their baseline assessment. Participants who do not attend their first session within 3 months are required to re-complete their baseline assessment; otherwise, they are no longer eligible to be enrolled.

To randomize at a group level, we adopted a more flexible covariate-adaptive randomization method known as Minimization [40, 41] on January 16, 2018, after 10 couples had been randomized using the prior approach. Minimization effectively addresses the scheduling difficulties inherent in couple-level block randomization by allowing sequentially recruited clusters of couples (e.g., 4–12 individuals) to be treated as single units, while offsetting imbalance in both individual- and couple-level prognostic variables [42]. Compared to stratification, Minimization can handle a larger number of prognostic factors and is more efficient in controlling imbalance in baseline variables than simple or restricted randomization [43]. In this trial, we set the biasing probability to 0.80 and used the range as the metric of imbalance in the minimization functioning.

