## Trial status

Recruitment for this trial began in August 2017 and completed in March 2021. In total, we randomized 128 couples (*N* = 256) to either 2GETHER (active condition) or PEONY (control). Follow-up assessments at 3, 6, 9, and 12 months post-intervention are ongoing. We acknowledge that most trial protocols are published prior to completion of enrollment and randomization. However, the onset of the COVID-19 pandemic during the course of recruitment resulted in changes to study protocols (see above) that we wanted to make sure to capture in this manuscript. Given that we were unsure when we would be able to return to our standard, pre-COVID-19 procedures (or whether additional changes would need to be made based on the evolution of the pandemic), we chose to complete this protocol paper after finishing enrollment because we believed it was the best way to most accurately capture all study procedures.

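### The stated power of 0.89 leaves out the session-group level of randomization and any loss of data, and the claim of sufficient power is not supported for the STI primary outcome

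*Protocol article*

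**What the plan says.** The Power analysis section first gives the superseded target: "At the onset of this trial, we aimed to randomize 200 dyads". It then reports a second calculation, made with WebPower for a two-arm cluster randomized trial with a within-couple ICC of 0.5, described as conservative. Of the method it says: "This method allowed us to account for the similarity between members of the same couple". The result is introduced by "With an adjusted goal of randomizing 125 dyads" and reads "power for the present study will be 0.89 to detect a medium-sized effect and 0.99 to detect a large effect". The section names no outcome, numeric effect size, significance level or allowance for loss. Trial status reports the achieved number: "In total, we randomized 128 couples".

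Randomization to the treatment arm says that the scheme changed on January 16, 2018, after 10 couples. From then on, once two to six couples had signed up for a session group, "all couples within that group are randomized to the active or control condition". Protocol changes after trial launch later permits a group consisting of one couple. It also says that participants due for baseline or 12-month assessment between the start of the pandemic in March and July 2020 had no STI test.

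Method and Table 1 make STI a primary outcome, tested only at baseline and 12 months. Analyses of primary aims compares it as two binomial proportions. The abstract's Discussion concludes that the couples were enrolled "with sufficient power to detect effects on study outcomes", with no outcome singled out.

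**The concern.** The second power analysis cites recruitment difficulties during the pandemic, so it was done after the move to group randomization. It still treats the couple as the unit that carries all the correlation. Couples who share an allocation, sessions and facilitators may resemble each other, and the calculation has no term for that. Nor has it one for missing 12-month data, although the article itself describes missed survey windows, withdrawal and a gap in STI testing.

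A single medium effect is also made to serve every outcome. For a binary outcome with a low event rate, an effect of that standardized size is a near-elimination of events. The abstract's statement covers the STI outcome without qualification, so a reader could take a non-significant STI result as evidence of no effect when the trial had little chance of detecting even a large relative reduction.

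**Working it through.** **1. The plan's own figure.** Inputs from Power analysis: J = 125 couples, n = 2 per couple, ICC = 0.5. Assumed, because not stated: standardized effects d = 0.5 (medium) and 0.8 (large), two-sided alpha 0.05, 1:1 allocation. For a two-arm cluster trial the test statistic is noncentral t with J − 2 degrees of freedom and

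λ = √( J·d² / [4·ICC + 4(1 − ICC)/n] ).

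The bracket is 4(0.5) + 4(0.5)/2 = 3.

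- d = 0.5: λ = √(125 × 0.25/3) = 3.23, df = 123, power 0.893.
- d = 0.8: λ = √(125 × 0.64/3) = 5.16, power 0.999.

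Both agree with the stated 0.89 and 0.99. A one-sided 5% test would give 0.94 for the medium effect and does not match. With the 128 couples randomized, the medium-effect figure is 0.900. The match requires all couples analysed and no correlation between couples in a session group.

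**2. Adding the randomized group.** With m couples per group and between-couple group ICC ρ, the design effect is 1 + 0.5 + 2(m − 1)ρ, λ = d·√(2J/4/design effect) and df = J/m − 2. The article gives neither ρ nor the mix of group sizes; both are assumed. For d = 0.5, 125 couples and no loss:

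| Couples per group | ρ = 0.01 | ρ = 0.05 | ρ = 0.10 |
|---|---|---|---|
| 2 | 0.88 | 0.87 | 0.85 |
| 3 | 0.87 | 0.84 | 0.80 |
| 6 | 0.84 | 0.76 | 0.66 |

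Example, m = 3 and ρ = 0.05: design effect 1.5 + 0.2 = 1.7, λ = 0.5 × √(62.5/1.7) = 3.03, df = 39.7, power 0.84.

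**3. Adding loss.** No rate is given, so a range is assumed. Losing 10, 20 or 30% of whole couples, with no group effect, gives 0.86, 0.82 and 0.76. Losing 15% of couples (106.25 left) with m = 3 and ρ = 0.05: λ = 0.5 × √(53.125/1.7) = 2.80, df = 106.25/3 − 2 = 33.4, power 0.77 (0.78 if the degrees of freedom are not lowered).

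**4. The STI outcome.** There are 125 individuals per arm, and the effective number at within-couple ICC 0.5 is 125/1.5 = 83.3. The normal approximation for two proportions is used, with the pooled variance under the null. The control rate and the halving are assumptions. Example, 10% against 5%: pooled rate 0.075, null SE √(2 × 0.075 × 0.925/83.3) = 0.0408, alternative SE √((0.09 + 0.0475)/83.3) = 0.0406, so power = Φ((0.05 − 1.96 × 0.0408)/0.0406) = Φ(−0.74) = 0.23.

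| Control rate | Halved to | Power, couple ICC 0.5 | Power, no couple correlation |
|---|---|---|---|
| 5% | 2.5% | 0.13 | 0.18 |
| 10% | 5% | 0.23 | 0.32 |
| 15% | 7.5% | 0.33 | 0.47 |
| 20% | 10% | 0.44 | 0.60 |
| 30% | 15% | 0.64 | 0.81 |

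These figures include no loss and no group effect; 15% loss lowers the ICC 0.5 column to 0.12, 0.20, 0.29, 0.38 and 0.57. Using 128 couples instead of 125 raises an entry by about 0.01 at most.

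For 80% power at couple ICC 0.5, the rate would have to fall from 10% to about 0.4%, or from 20% to about 5.6%. From 5%, even a fall to zero gives only 0.54. The approximation is rough at rates this near zero, but the order of magnitude is clear. A medium effect on the binary scale (Cohen's h = 0.5) is a fall from 10% to 0.5%, or from 20% to 4.5%.

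**The case against.** The strongest reply is that the calculation contains no mistake: 0.89 and 0.99 follow from their inputs. That stands, and the point is not one of arithmetic.

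Second, the loss from group randomization may be small. Ten couples were randomized before the switch, a group could hold two couples, and groups of one were later allowed. If the couple ICC of 0.5 really is conservative, it leaves room: with a true couple ICC of 0.3 (assumed), groups of 3 and group ICC 0.05, the design effect is 1 + 0.3 + 0.2 = 1.5 again and power is 0.88. A reader might infer that the power claim is false for the group-randomized design. The article does not support that, because the group ICC, the mix of sizes and attrition are not given.

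Third, deleting whole couples is pessimistic for individual-level outcomes. Participant retention keeps each partner in follow-up after a break-up. If 15% of individuals were lost independently (assumed), the information kept is [0.85² × 2/1.5 + 2 × 0.85 × 0.15]/(2/1.5) = 91%, and power is about 0.86. The growth models also use all four follow-up surveys for the behavioral outcome. Both arguments stand for that outcome. Neither helps STI, which has one follow-up test.

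Fourth, eligibility selects for risk behavior, so the STI rate may be high. At 30% with no couple correlation, power for a halving does reach 0.81. With the plan's own ICC of 0.5 it is 0.64.

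Finally, a journal article may leave power by outcome to the full protocol. True, and its absence alone would be no finding. The point rests on what is printed: a power figure whose clustering unit differs from the unit randomized, and a sufficiency claim without limits.

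**Conclusion.** The concern holds in a limited form. The power of 0.89 describes 125 independent couples with complete data. It does not describe a trial that mostly randomized session groups and missed some STI tests. For individual-level outcomes the overstatement is of unknown and possibly modest size: 0.84 to 0.88 under groups of 2 to 3, group ICC 0.01 to 0.05 and no loss. Power drops below 0.80 only with sufficiently larger groups, a larger ICC or added loss.

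For STI the abstract's claim is unsupported. Power to detect a halving is 0.13 to 0.44 at control rates of 5 to 20%, and at most 0.60 in that range even with no couple correlation. These results rest on assumed alpha, allocation, effect sizes, group ICC, group sizes, loss and STI rates; the article supplies none of them as numbers.

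Two further readings are tempting and do not hold. One is that 0.89 applies only to continuous outcomes: a binary outcome with a control rate of 40 to 60% and h = 0.5 also gives about 0.89 to 0.90. The other is that the couple-level outcomes are clearly underpowered. At a medium effect their power is 0.79 with 125 couples and 0.80 with 128, before loss or group clustering. Their rank is also inconsistent: Method says "Primary dyadic outcomes will be partner relationship agreement concordance and agreement breaks", while Table 1 lists both as secondary.

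**What to change.** Replace the single pair of figures with power for the 128 randomized couples, given separately for the behavioral and the STI primary outcomes. Include the randomized session group as a clustering level over a stated ICC range, using the actual distribution of group sizes, and make an allowance for loss, including the STI tests missed in 2020. Label every assumed input as assumed.

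For STI, give the minimum detectable difference over a range of control rates. State in advance that a non-significant result will be read as an estimate with its confidence interval and not as evidence of no effect. Qualify the sufficiency statement in the abstract accordingly.

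The cost is a recalculation, edited text and less favorable figures. No additional participants are needed, and with follow-up still under way the change can be made before results are known.
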